### Statistical analysis

Focus groups in study phase 1 will be evaluated by qualitative content analysis of data gained from the two focus groups. Details on study population will be provided by descriptive data analysis. In the RCT, intention to treat (ITT) analyses of primary data will be based on the available clinical data from all randomised participants after the nine-month follow-up. Missing data will be replaced by multiple imputations. For the primary endpoint, a mixed linear repeated measurement model (LMM) with the participant ID as random, group and time as fixed factor will be performed which is more robust against drop-outs than models without random factor [64] and uses the direct maximum likelihood as the statistical estimation procedure, which results in unbiased estimators under the missing-at-random-assumption [65]. We will use the closed test principle to evaluate differences between the means of groups. An additional analysis will be conducted on the per-protocol sample. The secondary endpoints alcohol-related problems, co-occurring substance use and help-seeking in those with transition to full-threshold alcohol use disorder, other mental health symptoms and quality of life will be examined in an exploratory manner with appropriate procedures, including subgroup analyses of gender of participants. Interim analyses will be performed after each wave of recruitment. Statistical analyses will be carried out with SPSS, Version 22 [66]. Associations between program usage patterns and reductions in alcohol use will be examined using latent class analysis (LCA) with Mplus, Version 5 [67].

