### Data collection

Participants will complete school-based online assessments at time of enrolment in the CP (t_0_) as well as at one and two years after enrolment (t_5_, t_6_) (Fig. 3). SP-specific assessments will be administered following enrolment in the SP (t_1_) and at the SP-specific follow-ups at three (t_2_), six (t_3_) and nine (t_4_) months after enrolment in SP3. All data will be collected online via central servers that are used for both the school-based assessments and the different interventions that are conducted via the ProHEAD online platform. Data will be handled in accordance with German legal regulations concerning data protection and data security (Data Protection Law of the Federal State of Baden-Wuerttemberg, Data Protection Law of the Free and Hanseatic City of Hamburg and German National Data Protection Laws) as well as EU General Data Protection Regulation. Data storage and transfer will be encrypted. All follow-up assessments will be conducted online via a password-secured website and will be recorded in the individual case report forms (CRF). An independent Data and Safety Monitoring Committee (DSMB) will oversee all aspects of data collection, handling and analysis. The DSMB will comprise independent researchers with expertise in research methodology, child and adolescent mental health, and technology-based alcohol interventions. Members of the DSMB will have their first meeting before inclusion of the first study participant.

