#### Primary outcome measure

For reasons of comparability, we chose to use the same primary outcome as in our previous study, testing the effectiveness of the original version of the web-based brief alcohol intervention without TIPs [24]. Therefore, the primary outcome is alcohol use in the past 30 days at nine-month follow-up as assessed by an index score for frequency and quantity of drinking and frequency of binge drinking calculated from the first three items of the Alcohol Use Disorders Identification Test (AUDIT-C) [41] adapted to assess drinking in the past 30 days. Frequency of alcohol consumption and frequency of having six drinks at one occasion (binge drinking) are assessed with response options ranging from 0 (never) to 4 (four or more times a week). The assessment of quantity of standard drinks consumed per typical drinking occasion (0 = one or two to 4 = ten or more) is supported by a graphical overview over units of alcoholic drinks defined as standard drinks. The AUDIT-C is validated in a sample of 14- to 18-year-old students in Germany [51].

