### Sample size and power calculation

Two focus groups will be realised in study phase 2 with five participants each. *N* = 20 at-risk alcohol-consuming children and adolescents will be recruited for the pilot testing of the newly designed TIPs. For the RCT, *N* = 15,000 children and adolescents will be assessed for eligibility (ProHEAD school sample). The estimated number of eligible participants for the ProWISE-TIP trial based on current data on the prevalence of risky alcohol consumption is *n* = 3270 [51]. Criteria for the allocation of participants to the five individual ProHEAD trials are based on latest scientific evidence. However, this is the first time that the overall algorithm is applied on a consortium-wide basis simultaneously screening for various mental health problems. Therefore, an intermediate data analysis will be conducted following completion of 10% of the screening assessments (*N* = 1500) in order to determine the actual allocation ratio to the five ProHEAD trials and to adjust the screening algorithm if necessary. Based on prior research, we expect that the ProWISE-TIP intervention reaches a small effect size (f = 0.10) when compared to the ProWISE-only condition and a medium effect size (f = 0.25) when compared to the psychoeducation control group [33, 35]. Thus, a total sample size of *N* = 1076 (intention-to-treat) (*n* = 269 in each trial arm) are needed (power = 0.80; alpha = 0.05, two-tailed; f = 0.10) in order to show superiority of the ProWISE-TIP intervention.

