### Compliance / Rate of loss to follow-up

According to recent reports on follow-up rates in trials testing web-based alcohol interventions and text-message-based interventions, follow-up data for 80% of randomised individuals are expected at the three-month follow-up, 75% at the six-month follow-up and 70% at the nine-month follow-up (primary endpoint) in the four trial arms [19, 24, 33]. These follow-up rates seem feasible because of the recruitment setting (schools) and the use of incentives. Participants will receive online gift vouchers after completion of each program-specific assessment at the follow-ups at three (€10), six (€20) and nine (€25) months.

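### As written, the primary mixed model yields a group effect averaged over visits, while the primary endpoint is the difference at nine months

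*Protocol article*

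**What the plan says.** The Primary outcome measure section states that "the primary outcome is alcohol use in the past 30 days at nine-month follow-up", measured by an index from the first three AUDIT items adapted to the past 30 days. The abstract gives the same timepoint. The section on loss to follow-up also attaches the primary endpoint to that visit, expecting "70% at the nine-month follow-up (primary endpoint) in the four trial arms".

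The outcome is collected repeatedly, with "SP-specific follow-ups at three (t_2_), six (t_3_) and nine (t_4_) months after enrolment in SP3" following the sub-project baseline.

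For the primary endpoint, the Statistical analysis section specifies "a mixed linear repeated measurement model (LMM) with the participant ID as random, group and time as fixed factor will be performed". On the comparison itself it says: "We will use the closed test principle to evaluate differences between the means of groups". The article names no group-by-time interaction, no visit at which the means are compared and no baseline covariate. It does not say whether baseline enters the model as one of the repeated outcomes.

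**The concern.** A model with main effects of group and time has one coefficient per group comparison, and that coefficient applies to every modelled visit. It is an average over the visits, so a test of it is not a test of the nine-month difference unless the effect is constant.

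Constancy cannot be taken for granted here. The prompts run for 12 weeks and so end at about the three-month visit, some six months before the endpoint. Fading after the prompts stop is plausible, though not certain, and a nine-month endpoint is chosen to show whether an effect lasts. An averaged test could support a nine-month claim on the strength of an effect seen only during or soon after prompting. It could also miss an effect that emerges late.

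This goes beyond detail that a journal article leaves out. The article states the random factor, the fixed factors, the estimation method and the multiplicity principle, and the factors it lists do not target the endpoint it lists.

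**Working it through.** **The plan's own figure.** The sample size section gives "power = 0.80; alpha = 0.05, two-tailed; f = 0.10", and says that "269 in each trial arm) are needed", a total of 1076. A one-way comparison of four groups with f = 0.10 (noncentral F, noncentrality N·f²) needs 1096, and has 79.3% power at 1076. The stated figure is therefore reproduced closely, as an omnibus test without dropout inflation. The present point does not alter it.

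**Inputs from the article.** 269 per arm; visits at 0, 3, 6 and 9 months; two-sided alpha 0.05; for follow-up, "follow-up data for 80% of randomised individuals are expected at the three-month follow-up, 75% at the six-month follow-up" and then 70%. For two groups, f = 0.10 corresponds to d = 2f = 0.20.

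**Assumptions, because the article gives no figures.** Outcome SD 1; equal within-person correlation ρ between visits, from 0.3 to 0.7; monotone dropout; the effect courses below.

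**Formulas.** With complete data and m visits, the group coefficient of the main-effects model is the plain mean of the visit effects, with SE = √[(2/n)(1 + (m − 1)ρ)/m]. With dropout it is a weighted mean, Σ wₖδₖ, with weights from generalised least squares. At ρ = 0.5:

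- Outcomes at 3, 6 and 9 months: weights 0.371, 0.329, 0.300; SE 0.080.
- Baseline also an outcome: weights 0.232, 0.209, 0.192, and the remaining 0.368 on baseline, where the expected difference is zero; SE 0.071.

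Worked example (ρ = 0.5, post-baseline visits, effect 0.20/0.10/0): 0.371 × 0.20 + 0.329 × 0.10 + 0.300 × 0 = 0.107. Then 0.107/0.080 = 1.34, and the two-sided rejection probability is 27%. The nine-month contrast estimates 0 and rejects in 5%.

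**Results over ρ = 0.3 to 0.7, with 80/75/70% retention.** Each cell gives the estimate and the rejection probability. The nine-month contrast comes from a group-by-visit model on the same outcomes, without a baseline covariate.

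| Effect at 3/6/9 months (SD) | Outcomes modelled | Main-effects model | Nine-month contrast |
|---|---|---|---|
| 0.20/0.10/0 | post-baseline | 0.11; 24–31% | 0; 5% |
| 0.20/0.10/0 | with baseline | 0.07; 13–19% | 0; 5% |
| 0/0/0.20 | post-baseline | 0.06; 10–14% | 0.20; 50–52% |
| 0/0/0.20 | with baseline | 0.04; 8–10% | 0.20; 51–56% |
| 0.20/0.20/0.20 | post-baseline | 0.20; 63–80% | 0.20; 50–52% |
| 0.20/0.20/0.20 | with baseline | 0.12–0.13; 35–54% | 0.20; 51–56% |

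The fifth row is the case in which the two targets agree, and there the averaged test has more power. In the last row the averaged estimate is diluted at every ρ, but the order of the power figures depends on ρ: at 0.3 the averaged test still has the higher power (54% against 51%).

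**The case against.** The strongest reply is that the sentence names the factors of the design and does not say that these are the only terms. A two-factor repeated-measures analysis is often described this way with the interaction understood. The sentence is also introduced as the analysis of the primary endpoint, which is fixed at nine months elsewhere. The full protocol or statistical analysis plan, not shown here, may well contain the interaction and the contrast. This part stands: the article does not exclude an interaction, and a reader who infers that the trial will certainly not test nine months goes further than the text. The inconsistency still remains, because an analyst following the published sentence would test group means with no visit attached.

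Three other stronger readings are tempting, and the article does not support them.

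- **That the model always dilutes the effect or loses power.** With post-baseline outcomes and a constant effect it does neither. On complete data at ρ = 0.5, the averaged test of a constant 0.20 SD has 81% power, against 76% for a baseline-adjusted nine-month contrast and 64% for an unadjusted one.
- **That the model imposes equal correlation between visits.** The article names a random participant factor but is silent on residual covariance, which is ordinary analysis-plan content. Equal correlation is used above only to put numbers on the point.
- **That the effect will have vanished by nine months.** The Background cites a 12-week text-message study in young adults with effects still present at nine months. Complete fading is one plausible course, not the expected one.

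**Conclusion.** The point stands as a mismatch between the stated endpoint and the stated model. Read as written, the primary test concerns an effect averaged over visits, which coincides with the nine-month difference only if the effect is equal at every modelled visit.

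That conclusion about the target does not depend on the assumed correlation; the size of the consequence does. With a 0.20/0.10/0 SD course, a test meant to reject in 5% of trials rejects in 24–31% (post-baseline outcomes) or 13–19% (baseline included). With a 0/0/0.20 course, less than a third of the nine-month effect is recovered (0.06 or 0.04 of 0.20). These figures rest on the assumed SD, correlation range, dropout pattern and effect courses, and on the model having no interaction. They show what the wording permits and do not forecast what the trial will find. No general gain in power is claimed for the correction.

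**What to change.** Revise the primary analysis statement, and reconcile it with the analysis plan if that already says so:

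- Model the three-, six- and nine-month outcomes with group, categorical visit, group-by-visit, baseline adapted AUDIT-C and baseline-by-visit as fixed effects, and an unstructured within-participant covariance.
- Define the primary test as the between-group contrast at nine months from that model, and apply the closed test procedure to those contrasts.
- Report the visit-averaged effect as secondary.

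Baseline then enters as a covariate and not as an outcome, which settles its handling. On complete data, the adjustment reduces the SE of the nine-month contrast from √(2/269) = 0.086 to √(2(1 − ρ²)/269), which is 0.075 at ρ = 0.5.

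The cost is a sentence or two of text and a few more model parameters, with no change to data collection. The real downside is lower power than the averaged test if the effect is truly constant over the follow-up visits. That is the price of testing the endpoint that the protocol names.

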### Aims

In this trial we will further develop a previously evaluated youth-specific, web-based, single-session, brief motivational alcohol intervention [24] to increase positive effects on reductions in alcohol consumption and alcohol-related harm in children and adolescents aged ≥ 12 years identified as risky drinkers. Specifically, we will integrate text-message-initiated individualised prompts (TIPs) following the initial delivery of the web-based, single-session, brief motivational intervention (ProWISE intervention) and test this version of the intervention in a randomised controlled trial (RCT). Main goals of this trial are: (1) development of a user-centred, time-efficient and youth-specific text-message-initiated technique for delivering highly individualised prompts assessing drinking intentions and actual alcohol use and providing individualised feedback; (2) pilot testing of feasibility and acceptability of the new intervention components (i.e. TIPs) and their refinement according to results from the pilot testing and evaluation of focus group interviews; and (3) evaluation of effectiveness of the TIPs as boosters for the ProWISE intervention in a four-arm randomised controlled design.

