### Participants

The project will utilize a large-scale school-based sample of children and adolescents (*N* = 15,000 children and adolescents, grades 6–13, aged ≥ 12 years), recruited in five regions of Germany (Hamburg, Heidelberg, Leipzig, Marburg, Schwäbisch Gmünd). In the central project (ProHEAD consortium), online assessments of a broad variety of mental health problems and health-risk behaviours will be conducted at baseline and at two annual follow-ups. Following the baseline assessment, children and adolescents will be identified as either currently ‘healthy’, ‘high-risk’ (including subthreshold mental health problems and diverse health-risk behaviours) or having ‘mental health problems’ (which includes clinically relevant levels of psychopathology and/or indicators of threat to self and others). Based on these screening profiles, children and adolescents will be allocated to one of five programs according to their individual needs, i.e. increasing face-to-face mental help-seeking in children and adolescents with a screening result at baseline indicating mental health problems (SP1) [36], preventing eating disorder symptoms in children and adolescents with a screening result at baseline indicating a risk for the development of an eating disorder (SP2) [37], reducing alcohol misuse in children and adolescents with a screening result at baseline indicating risk for the development of alcohol misuse (SP3, ProWISE-TIP trial), preventing depressive symptoms in children and adolescents with a screening result at baseline indicating a risk for the development of depression (SP4) [38], promoting mental health and preventing mental health problems in children and adolescents with a screening result at baseline indicating no mental health problems (SP5) [39]. All programs provide online information as well as additional modules such as prompts or chat counselling with mental health professionals.

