### Inclusion and exclusion criteria

Children and adolescents (1) in grades 6–13 aged ≥ 12 years, (2) with a positive screening result for at-risk alcohol use based on the CRAFFT-d screening tool (≥ 2) [40], (3) and written informed consent from both participant and legal guardian are eligible for inclusion in the ProWISE-TIP trial. Children and adolescents with (1) current alcohol use disorder according to the Alcohol Use Disorders Identification Test (AUDIT) (≥ 20) [41] or (2) current psychiatric disorders, (3) illiteracy, (4) no possession of a mobile phone, no access to the Internet or no sufficient German language skills will be excluded from participation in the ProWISE-TIP trial (Fig. 1). Children and adolescents with a total score of ≥ 20 in the AUDIT [41] or a total score of 20–40 points on the Strengths and Difficulties Questionnaire (SDQ) [42] or a score above the defined thresholds for one of its sub-scales: emotional symptoms (scores: 7–10), conduct problems (scores: 5–10), hyperactivity/inattention (scores: 7–10), peer relationship problems (score > 5) will be excluded from the ProWISE-TIP trial and included in SP1 of the ProHEAD consortium. Children and adolescents with a negative screening result for risky alcohol use (CRAFFT-d score < 2) will be included in SPs 2, 4 or 5 of the ProHEAD consortium, depending on which inclusion criteria they meet. Study participants fulfilling inclusion criteria for more than one SP addressing children and adolescents at risk for developing an eating disorder, alcohol-related problems or depressive symptoms (SP2–4) will be allocated randomly to one SP (see CP study protocol [36] for details). There are no restrictions for study participants to take up concomitant care outside ProHEAD.

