### Recruitment and randomisation

Participants for the trial will be recruited through the ProHEAD infrastructure with five centres (Heidelberg, Hamburg, Leipzig, Marburg, Schwäbisch Gmünd) actively recruiting and drawing children and adolescents from a national school-based sample. For a detailed description of the recruitment process, please refer to Kaess et al. [36]. After enrolment in the central project, study participants will be allocated to one of the five SPs according to their screening result (Fig. 1). All participants receive an e-mail containing a link to an encrypted webpage where they can register to the respective SP. Participants with a positive screening for at-risk alcohol use are invited to take part in the ProWISE-TIP trial and referred to the SP-specific online baseline assessment (Fig. 3). After completion of the assessment, participants will be randomised to one of the four study arms (A) ProWISE plus TIP for 12 weeks (ProWISE-TIP); (B) ProWISE plus TA for 12 weeks (ProWISE-TA); (C) ProWISE intervention only (ProWISE only); (D) web-based psychoeducation on alcohol use in childhood and adolescence (control group). Randomisation is conducted automatically by the computer program on the basis of predefined lists and following a permutated block design. Randomisation will be stratified by age and gender. Once participants have completed the trial-specific online baseline assessment, they automatically receive a computer-generated e-mail containing a link to access the online content in their respective trial condition.

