
Additional secondary outcomes will be assessed in the school-based follow-ups at one and two years after enrolment. Help-seeking will be assessed using an adapted version of the Actual Help-Seeking Questionnaire (AHSQ) [56], which assesses actual help-seeking behaviour by listing potential help sources and measuring whether help has been sought from the respective sources within a specified time-period for a specified problem. The 13-item questionnaire comprises three subscales: whether informal help has been sought; whether formal help has been sought; and whether no help has been sought. Response options are 0 = ‘no’, 1 = ‘yes, in the past 12 months’ and 2 = ‘yes, but longer ago then 12 months’. The Actual Help-Seeking Questionnaire (AHSQ) is validated in a sample of 16- to 19-year-old students [56]. Mental health symptoms will be assessed using the Strengths and Difficulties Questionnaire (SDQ), a self-report screening questionnaire for children and adolescents aged 2–17 years [42]. The four subscales (emotional, conduct, hyperactivity and peer problems), each scored on a scale of 0–10, will be assessed. Higher scores indicate a higher level of psychopathology. Quality of life will be assessed using the KIDSCREEN-10 [57]. The KIDSCREEN is an international cross-culturally comparable quality-of-life assessment instrument validated for children and adolescents aged 8–18 years. The KIDSCREEN-10 index comprises 10 items, which provide a global measure of health-related quality of life. Items are answered on a 5-point response scale and are coded in a way that higher values indicate better quality of life. Furthermore, program usage patterns (frequency of replies to TIPs, duration, completion) based on log-file data will be analysed.

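### Help-seeking is a secondary endpoint in those who develop alcohol use disorder, a subset formed after randomisation, so an arm contrast within it is not a randomised comparison

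*Protocol article*

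**What the plan says.** In the protocol article, Statistical analysis names "help-seeking in those with transition to full-threshold alcohol use disorder" as one of the secondary endpoints of the randomised trial. These endpoints "will be examined in an exploratory manner with appropriate procedures, including subgroup analyses of gender of participants". The section gives no other statement on how help-seeking is analysed.

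Four other places bear on the point:

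- **Inclusion and exclusion criteria:** an AUDIT score of 20 or more, which the article treats as current alcohol use disorder, excludes a child from this trial and leads to sub-project 1 instead.
- **Recruitment and randomisation:** allocation follows the trial's own baseline assessment: "After completion of the assessment, participants will be randomised to one of the four study arms".
- **Secondary outcome measures:** "Additional secondary outcomes will be assessed in the school-based follow-ups at one and two years after enrolment". Help-seeking, measured with an adapted Actual Help-Seeking Questionnaire, is one of these outcomes. The section does not limit it to participants who have developed a disorder.
- **Aims:** the intervention is meant "to increase positive effects on reductions in alcohol consumption and alcohol-related harm in children and adolescents aged ≥ 12 years identified as risky drinkers". The Participants section describes the sub-project's purpose as "reducing alcohol misuse in children and adolescents with a screening result at baseline indicating risk for the development of alcohol misuse".

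**The concern.** Participants enter without alcohol use disorder, so anyone counted as having progressed to it is identified at a follow-up after allocation. Progression is also what the interventions try to prevent. Membership of the subset is therefore partly a result of the arm.

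Randomisation balances the arms as allocated. It does not balance those who later progress. If an intervention prevents the milder cases, those who still progress in that arm are more severe on average. If more severe cases seek help more often, that arm shows more help-seeking although nobody's help-seeking has changed. If the severe cases are the ones prevented, the opposite appears.

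At stake is what can be concluded from a secondary endpoint: a difference in the subset could be reported as an effect on help-seeking, in either direction, when there is none.

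**Working it through.** **Is the subset post-randomisation?** Disorder is excluded at screening, allocation follows the baseline assessment, and help-seeking is measured at one and two years. So the subset is formed during follow-up, after allocation.

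**Is it affected by arm?** The stated aim is to reduce consumption, harm and misuse. If the intervention works as intended, the arms should differ in how many, and which, participants progress.

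**How large could the distortion be?** The article states no figure on this point to reproduce. It gives no transition rate, no help-seeking rate and no link between severity and help-seeking, so all of these are assumed.

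Model:
- Latent severity U and noise e are independent, each N(0,1).
- A participant transitions if U + e − effect > 2.3. In control the effect is 0.
- The probability of seeking help is 1/(1 + exp(1.5 − U)), with no term for arm.

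U + e has standard deviation √2 = 1.414, so the transition rate is 1 − Φ((2.3 + effect)/1.414):
- control: 1 − Φ(1.626) = 5.2%
- intervention, effect 0.5: 1 − Φ(1.980) = 2.4%

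Help-seeking among those who transition is the probability above, averaged over U with the transition probability as weight.

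| Scenario | Transition | Help-seeking in subset | Help-seeking, all randomised |
|---|---|---|---|
| Control | 5.2% | 49% | 22% |
| Intervention, effect 0.5 | 2.4% | 54% | 22% |
| Intervention, effect 0.28 (0.2 SD of U + e) | 3.4% | 52% | 22% |
| Intervention, effect 1.0, only where U > 1 | 2.3% | 41% | 22% |

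The third row takes the article's small effect, f = 0.10, as d = 2f = 0.2 on the liability scale; the spurious gap is about 3 points. In the last row only severe participants are protected, and the sign reverses.

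A second model (logistic transition, control rate 5% to 20%, odds ratio for transition 0.7 to 0.5) gave spurious gaps of about 0.5 to 3 points. One of its cases is 45.3% in control and 48.2% in intervention.

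The sign change can also be seen by hand. Suppose 27 control participants transition: 13 who would do so in either arm and 14 whom the intervention would prevent.
- Prevented cases milder (15% seek help, the others 50%): control (13 × 0.50 + 14 × 0.15)/27 = 31.9%, intervention 50%.
- Prevented cases more severe (50% seek help, the others 15%): control (13 × 0.15 + 14 × 0.50)/27 = 33.1%, intervention 15%.

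**How many would be analysed?** There are 269 per arm (Sample size and power calculation). The article gives 70% follow-up at nine months and no figure for one or two years; applying 70% there is an assumption.

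| Assumed transition | Per arm, 269 × rate | With 70% followed up |
|---|---|---|
| 5% | 13 | 9 |
| 10% | 27 | 19 |
| 20% | 54 | 38 |

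In the illustration, 269 × 5.2% ≈ 14 control and 269 × 2.4% ≈ 6 intervention participants would be analysed. The standard error of the difference is √(0.487 × 0.513/14 + 0.538 × 0.462/6) = 0.24, or 24 points, against a bias of about 5 points. Subgroup analyses by gender would divide these numbers again.

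**The case against.** The strongest case against is that the article does not state the flawed analysis outright. It names no between-arm test for help-seeking, it calls the secondary endpoints exploratory, and an article may leave the method to a fuller document. Purely descriptive reporting in those who transition would fit the sentence as written. This stands in part. A reader might infer that help-seeking will be compared between arms only in this subset, but the text says neither "compared" nor "only". What remains is that the article itself writes the subset into a secondary endpoint of a randomised trial and mentions no analysis in everyone.

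A reader might also see a contradiction with Secondary outcome measures, which sets no restriction. Measuring everyone and examining a subset is not a contradiction. Health service utilisation is also recorded for participants generally (Health economic measures), so care use as a whole is not confined to the subset.

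The restriction has a rationale too, because seeking help matters most for those with a disorder. That supports a descriptive table, not a causal contrast.

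Finally, the bias is modest in most scenarios and smaller than the sampling error. That makes a confident false claim unlikely, but it also means the subset contrast could tell little even without bias. The exploratory label tempers the strength of any claim; it does not restore comparability of the arms.

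**Conclusion.** The point holds in a limited form. Any between-arm contrast of help-seeking among those who progress to alcohol use disorder is non-randomised, because the subset forms after allocation through an event the interventions target. This follows from the article's own entry criteria, timing and aims, and needs no assumed rate.

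The size does rest on assumptions. The spurious gap was about 0.5 to 5 points in the moderate scenarios, larger in the deliberately extreme ones, and of either sign. The subset would hold roughly 13 to 54 per arm before drop-out if 5% to 20% progress.

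A reader might infer that the trial's main conclusion is at risk. It is not: the primary outcome is analysed in all randomised participants, and no confirmatory claim rests on help-seeking.

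**What to change.** Add one sentence to the Statistical analysis section, for example: *Help-seeking will be compared between arms in all randomised participants; among those who progress to alcohol use disorder it will be reported by arm as description only, without a between-arm test, together with the proportion progressing in each arm.*

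A composite defined for everyone, such as progression without formal help sought, is optional. It combines the effect on progression with the effect on help-seeking and must be read that way.

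The cost is close to nil: the questionnaire is already planned without the restriction, and no sample size, visit or instrument changes. The downside is that help-seeking in everyone is less specific to those with a disorder; the descriptive table covers that.
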